#### Phase III

The final stage of the protocol will consist of a double-blind randomized controlled phase-III trial in which a large group of patients with insomnia recruited from the Sleep Unit of the Hospital Universitario de la Ribera, as well as from collaborating medical institutions will voluntarily enroll in an 8-weeks personalized and supervised cognitive training intervention. The medical team will inform those patients who meet the inclusion criteria of the possibility of voluntarily participating in the experiment. Those interested will be put in contact with the researchers, who will interview them individually. In this first contact, all the information regarding the study will be provided. Patients who agree to participate will complete the necessary legal documentation and informed consent and be included in the study.

A complete evaluation will be carried out at the beginning (pretest) and at the end of the intervention (post-test) using the materials and instruments also used in the phase-II study. The pretest will collect baseline data about sleep problems and cognitive skills, together with sociodemographic information. Standardized batteries and tests will be used to measure the general neurocognitive state and the emotional state, together with specific tests and measurements of the pattern and quality of sleep, and tests that measure health-related quality of life. All variables will be measured objectively (i.e., direct test scores) and subjectively (i.e., what the patient or her close associates express). The post-test will collect data on sleep problems and cognitive skills, but no additional sociodemographic data will be needed (see *Instruments and Outcome Measures* section for a description of the tools). Having already established the safety of the protocol in the phase-I and phase-II studies, no information will be collected in this regard in the phase-III trial.

Next, the CCT intervention will be carried out. This will be done through the CogniFit online platform so that each participant will access it from home using a personal computer or smart device. The training will last for a total of 8 weeks, with five training days per week. This way, a total of 40 training sessions are expected. The duration of the sessions will be determined by the maximum tolerated training time resulting from the phase-I trial. Since this process will be autonomously managed by each participant, they will be contacted periodically (a minimum of two phone calls per week) to ensure adherence and check that they have not had any incidence. The platform will record participants’ performance, providing researchers with real-time feedback on the performance and adherence of each participant.

Participants will be randomly assigned to one out of two groups (control/experimental). The experimental group will complete a personalized CCT intervention based on CogniFit’s Personalized Online Training, including a series of games and activities targeting attention, memory and executive functions. The difficulty level of each of the activities will dynamically change to match the cognitive profile of each participant on each training day. By automatically adjusting the activities’ difficulty and requirements according to each participant’s performance, cognitive taxing is adapted and a maximum cognitive effort is always required. Similar to Haimov and Shatil (2013), the active control group will complete a series of painting activities specifically designed not to result cognitively demanding and to maintain a low complexity level and constant difficulty throughout the intervention. These activities will not target the intended cognitive processes (namely, they will target orthogonal unrelated aspects). Participants will be randomly assigned to either the experimental or control group, with the experimenters and the patients being fully blind to the group classification.

After post-test data collection, and prior to statistical analyses, all variables will be checked for normality of distribution, and plots will be visually inspected for asymmetry and kurtosis. Then, descriptive statistics will be obtained to provide an overview of the sociodemographic and clinical characteristics of the participants. To examine intervention effectiveness, the changes in all outcome measures from baseline (pretest) to post-intervention (post-test) will be analyzed. Differences in primary outcomes and secondary outcomes will be analyzed through linear mixed models for repeated measures. Models will assess within and between-group differences before and after the intervention. The Group factor (experimental, control) will be included as an independent variable, together with Time (pre-test at baseline, post-test after the intervention). Sociodemographic factors such as gender and age will be used as moderators. Dependent variables will be sleep quality, insomnia severity, quality of life, cognitive abilities, executive function, depressive symptoms, anxiety symptoms, and worrying. To isolate the variable that better explains the model, a hierarchical regression analysis will be conducted with the sleep quality improvements as the dependent variable and the cognitive improvements as the independent ones. This hierarchical regression analysis will be also useful to evaluate the impact of the adherence to the training in the whole sample of participants, regardless of whether they have effectively completed the intervention or not (i.e., cases of attrition or incomplete sessions). The hierarchical regression analysis with the sleep quality improvement as the dependent variable will follow a stepwise approach in which sociodemographic factors will be added in a first step, the data corresponding to the adherence to the treatment (namely, number and length of the completed sessions) in a second step, and the cognitive data from the BRIEF-A and the Cognitive Assessment Battery CAB™ as a third and final step.

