The first cohort of participants (*N* = 3) will then start the phase I testing protocol. All participants will complete CogniFit Personalized Online Training, consisting of individual sessions in which three brain training games with a duration of around 5 min each need to be completed. The CCT will train six fundamental cognitive skills associated with the domains of memory, attention, perception and coordination: naming, working memory, non-verbal memory, visual perception, response time, divided attention and inhibition. The three participants from the first cohort will individually complete a 15-min training session under the supervision of a researcher from the team and a clinical psychologist. After finishing the session, they will complete a fatigue and safety evaluation questionnaire aimed at obtaining information about potential side effects and adverse events associated with the clinical process (see *Instruments and Outcome Measures* section). In case no side effects or adverse events are reported, a dose escalation will be implemented, and participants will then continue with a new training session of similar characteristics, structure and duration. The fatigue and safety questionnaire would be repeated right at the end of this new session, and the protocol would cyclically continue until the supervising researchers decide not to continue with an additional session because of having reached the dose-limiting toxicity level. If one participant from the cohort reports extreme fatigue levels (scores of 9 or 10 on the scale described below) or side effects or adverse events (see the questionnaire below) with a certain dose level (level i), a new cohort of three participants would start the protocol with the same dose level. If no other participant from the 3 + 3 cohort reports extreme fatigue, side effects or adverse events, the procedure would restart for a new cohort of three participants at the next dose level (level i + 1). However, if more than one participant from the 3 + 3 pool reports any of the outcomes, the maximum tolerated dose of the CCT would be set at level i-1. If two or more participants from the first cohort report extreme fatigue levels, or side effects, or adverse events with a certain dose level (level i), the maximum tolerated dose of the CCT would be set at level i-1.

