#### Phase II

This trial will include a different group of 20 patients from the same hospital who meet the inclusion criteria described above, who will also sign the corresponding consent forms prior to initiation of collaboration. After having set the maximum tolerated training time per session in the phase I trial, a 15-day phase-II trial will be designed to ascertain the effectiveness of the CCT in the absence of adverse events or side effects.

To this end, 20 patients from the Sleep Unit of the Hospital Universitario de la Ribera (Spain) will be recruited and they will first complete an initial session (Day 1) that will serve to collect baseline data about their sleep problems and their cognitive skills, as well as about their sociodemographic information. As in the phase I trial, they will complete the general cognitive and psychological evaluation lasting for around 60 min (see Instruments and Outcome Measures section).

The day after the initial evaluation (Day 2), participants will be asked to visit the Sleep Unit again to complete the first training session with the CCT. The duration of the training session will be determined by the results of the phase I trial. Participants will complete this training session using either a tablet, a PC or a laptop, accompanied by the research and clinical team. Right at the end of the session, and in order to assess the safety of the intervention, participants will also complete the same safety questionnaire as in the phase I trial. In case any participant at any moment would report potential adverse events in any of the safety questions, the clinical psychologist would immediately interview them in order to classify the side effect or adverse event according to its seriousness following the criteria and elements adapted from the Patient-Reported Adverse Drug Event Questionnaire (de Vries et al., 2013).

The protocol would then continue the next day (Day 3) with a full assessment identical to that of the first session. The day after (Day 4) would consist of the repetition of the training session of Day 2. This way, and alternating assessment and training sessions, participants will complete a 15-day cycle that will start and end with a full assessment (Day 1 and Day 15), and that will include eight different evaluation or test points (Day 1, Day 3, Day 5, Day 7, Day 9, Day 11, Day 13, and Day 15) and seven training sessions (Day 2, Day 4, Day 6, Day 8, Day 10, Day 12, and Day 14).

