The results of the effectiveness of the CCT will be evaluated using linear mixed models for repeated measures, analyzing differences in the primary and secondary outcomes described below. This will provide a first approach to and statistical validation of the usefulness of the CCT to alleviate the cognitive, psychological or medical symptoms of insomnia in the selected sample by determining the minimum number of training sessions needed to observe a significant change. Besides, quantitative and qualitative analysis of the results of the safety questionnaires will help us determine the safety of the intervention program.

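### Phase III stops collecting safety information at the stage where home training, five days a week for 40 sessions, and a control group first appear

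*Protocol article*

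**What the plan says.** All references are to the protocol article, Methods and Analyses.

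- **Phase I** is supervised and enrols cohorts of three. Patients complete a training session of about 15 minutes and then a fatigue and safety questionnaire. If nothing is reported they continue with another session, and "The fatigue and safety questionnaire would be repeated right at the end of this new session". The result is a maximum tolerated time per session.
- **Phase II** enrols 20 other patients at the Sleep Unit. On session length: "The duration of the training session will be determined by the results of the phase I trial". Each patient has "seven training sessions (Day 2, Day 4, Day 6, Day 8, Day 10, Day 12, and Day 14", with a full assessment on the days between. The first training session is accompanied by the research and clinical team, and the later ones are described as repetitions of it. On safety: "quantitative and qualitative analysis of the results of the safety questionnaires will help us determine the safety of the intervention program". Neither Phase I nor Phase II is described as having a control group.
- **Phase III** randomises at least 60 patients per group to cognitive training or painting activities. On session length: "The duration of the sessions will be determined by the maximum tolerated training time resulting from the phase-I trial". Participants train at home and manage the sessions themselves for 8 weeks, "with five training days per week. This way, a total of 40 training sessions are expected". Contact is by telephone: "a minimum of two phone calls per week) to ensure adherence and check that they have not had any incidence". The platform records performance and adherence.
- On safety in Phase III: "Having already established the safety of the protocol in the phase-I and phase-II studies, no information will be collected in this regard".

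**The concern.** The no-collection sentence is a stated rule, so it cannot be put down to the article being a condensed account. Its justification is that safety will already have been settled, but Phases I and II do not test the regimen that Phase III uses. Three things are new in Phase III: the cumulative exposure, training without staff in the room, and a comparison group.

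The comparison group matters most for interpretation. Patients with insomnia are often tired for reasons unrelated to training, so a fatigue report is hard to attribute without controls. Phase III is the only stage that could compare fatigue and adverse events between arms, and there the plan sets the collection aside.

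What is at stake is patient safety and what the trial can report on harms. The efficacy analysis is not affected.

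**Working it through.** **1. The plan's own figures.** Phase III: 8 weeks x 5 days = 40 sessions, as stated. Phase II: days 2 to 14 in steps of two, (14 - 2)/2 + 1 = 7 sessions, as stated.

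**2. Exposure side by side.**

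| | Phase II | Phase III, experimental arm |
|---|---|---|
| Patients | 20 | 60 (minimum) |
| Sessions per patient | 7 | 40 |
| Sessions per week | 3.5 (alternate days) | 5 |
| Total sessions | 20 x 7 = 140 | 60 x 40 = 2,400 |
| Setting | Sleep Unit, accompanied | home, self-managed |
| Control group | none described | yes |

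Ratios: 40/7 = 5.7 per patient, 5/3.5 = 1.4 per week, and 2,400/140 = 17 in total.

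**3. What 20 patients can show.** If a share p of patients is affected, the chance that none of n is affected is (1 - p)^n. The documents give no value for p, so I assume a range.

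| Assumed p | None of 20 affected | None of 60 affected |
|---|---|---|
| 2% | 67% | 30% |
| 5% | 36% | 5% |
| 10% | 12% | 0.2% |

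With no affected patient among n, the one-sided 95% upper limit is 1 - 0.05^(1/n). This is 13.9% for n = 20 and 4.9% for n = 60. These figures reflect sample size only. They do not measure the effect of repeated exposure.

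**4. Longer exposure, as an illustration.** Assume a constant, independent risk h per session. The risk over k sessions is 1 - (1 - h)^k.

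| Assumed h | Risk over 7 sessions | Risk over 40 sessions | Phase II sees at least one case | Expected cases among 60 in Phase III |
|---|---|---|---|---|
| 0.1% | 0.7% | 3.9% | 13% | 2.4 |
| 0.5% | 3.4% | 18.2% | 50% | 10.9 |
| 1% | 6.8% | 33.1% | 76% | 19.9 |

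The values of h are assumptions, and the documents do not suggest that any of them is true. The table shows that seven sessions in 20 patients can look clean while 40 sessions in 60 patients produce several cases.

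**5. The two Phase III statements compared.** One says that no safety information will be collected. The other has staff telephone every participant at least twice a week and check for incidents, which is at least 2 x 8 = 16 calls per patient. A caller who hears of an adverse event on such a call has received safety information, and the plan's wording says it is not collected. Adherence data, which enter the hierarchical regression as number and length of completed sessions, show that sessions were missed but not why.

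**The case against.** The strongest reply has four parts.

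- *Phase II covers safety at the same session length.* This is correct. A reader might infer that Phase III session length rests on Phase I alone, with Phase II ignored. The documents do not support that. The Current Proposal gives Phase II the task of validating safety, the objectives name tolerability and safety, and Phase III relies on both earlier phases. No explicit rule for revising the length is stated, but that is a narrower matter and I do not press it.
- *Phase III is not unmonitored.* Also correct. A reader might infer that nothing about harm could come to light. The calls check for incidents, the platform gives real-time adherence data, and the Phase III overview describes the intervention as supervised. The sleep, insomnia, mood, anxiety, worry and quality-of-life scales are taken before and after training and analysed by group, so they would partly show a net worsening. They do not capture fatigue after sessions, adverse events during the 8 weeks, or the reason a participant stopped.
- *The sentence may only drop the questionnaire.* It closes the paragraph on the pretest and post-test batteries, so it could mean that the Phase I and II safety questionnaire is not repeated there. That reading is possible, but the words are general, and the conflict with the calls still needs resolving.
- *The risk is low.* Nothing in the documents points to material harm from these games, and the rates above are assumptions. This argues for a light method of collection. It does not justify collecting nothing, since the authors themselves treat extreme fatigue as dose-limiting in Phase I.

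**Conclusion.** The point stands as a minor one. The plan justifies collecting no safety information in Phase III by reference to phases that do not test 40 self-managed home sessions at five per week and that have no described control group. The same section plans calls that ask about incidents, so the plan is also inconsistent with itself.

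The differences in exposure (5.7 times per patient, 17 times in total) follow from the plan's own numbers, assuming full recruitment and completion. The detection probabilities rest on assumed event rates. Sample size, error rates and the efficacy analyses are unaffected. The documents do not support a conclusion that the training is unsafe or that the session length is wrong.

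**What to change.** Replace the no-collection sentence in the Phase III section with a statement to this effect:

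- At the planned calls, in both arms and throughout all 8 weeks, staff ask and record the existing 0-10 fatigue item and the two yes/no safety questions from Safety Outcome Measures.
- The items refer to the period since the last call, because they now refer to the present moment and the session just finished. They speak of the activities rather than of computerized cognitive training, so that the wording fits both arms and protects the blinding.
- A fatigue score of 9 or 10, or a yes to either question, leads to the interview and classification already described for a yes.
- The reason for any discontinuation is recorded, and all results are summarised by arm.

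Collection should run for the full 8 weeks, because the later weeks hold the cumulative exposure that Phase II did not reach.

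The cost is a few minutes per call. There are at least 16 calls per patient with three questions each, so 16 x 3 = 48 short answers. For 120 patients that is 16 x 120 = 1,920 calls, all already planned, plus an interview for each positive answer. No visits are added. Asking may raise symptom reporting, similarly in both arms if the wording is neutral. Ratings over a period will not be directly comparable with the post-session ratings of Phases I and II.

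I do not propose a Phase II threshold for shortening sessions. The safety question counts any side effect, harmful or not, so the triggering event would first need a definition. A shortened session would also be one whose efficacy Phase II had not tested.

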#### Secondary Outcome Measures

##### Executive Functions

The Behavior Rating Inventory of Executive Function-Adult Version (BRIEF-A) will be used. The BRIEF-A is a standardized measure that captures views of an adult’s executive functions or self-regulation in his or her everyday environment. Only the self-report format will be used. The BRIEF-A comprises 75 items within nine theoretically and empirically derived clinical scales that measure various aspects of executive functioning; Inhibit, Self-Monitor, Plan/Organize, Shift, Initiate, Task Monitor, Emotional Control, Working Memory, Organization of Materials. The clinical scales form two broader indexes: Behavioral Regulation (BRI) and Metacognition (MI), and these indexes form the overall summary score, the Global Executive Composite (GEC). It also includes three validity scales (Negativity, Inconsistency, and Infrequency). It takes approximately 10–15 min to administer. All 75 items are rated in terms of frequency on a 3-point scale: 0 (never), 1 (sometimes), 2 (often). Raw scores for each scale are summed for the total score.

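### Phase III is described as fully blind and as measuring every variable objectively; the procedures and instruments described support neither statement, and all primary outcomes are self-reported

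*Protocol article*

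**What the plan says.** All the statements on blinding stand in the Phase III section of the protocol article.

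- The trial is labelled "a double-blind randomized controlled phase-III trial", and participants are assigned "with the experimenters and the patients being fully blind to the group classification".
- The training platform records performance, "providing researchers with real-time feedback on the performance and adherence of each participant". Participants are also phoned at least twice a week about adherence and incidents.
- In the experimental arm, "The difficulty level of each of the activities will dynamically change to match the cognitive profile of each participant on each training day". The active control arm paints, at low complexity and constant difficulty.
- On what patients are told before consent: "In this first contact, all the information regarding the study will be provided".
- On measurement: "All variables will be measured objectively (i.e., direct test scores) and subjectively". The sentence goes on to define subjective measurement as what the patient or close associates express.

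The instruments follow under Instruments and Outcome Measures. For the BRIEF-A, "Only the self-report format will be used".

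**The concern.** Two claims that a reader would use to judge the credibility of the result do not match the procedures and instruments in the same article.

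The first is full blinding of both experimenters and patients. Performance data from adaptive games and from constant-difficulty painting are unlikely to look alike, so whoever follows them can probably tell the arm. A patient cannot be unaware of whether they play games or paint.

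The second is objective measurement of every variable. No objective sleep or quality-of-life measure is listed.

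The two belong together. When an outcome is a questionnaire filled in by the patient, blinding of the patient is the main protection against a difference that arises from expectation. If blinding is only partial and the outcome is self-reported, a between-arm difference in PSQI or ISI may reflect expectation as well as training. A reader who trusts both statements would credit the difference to cognitive training with more confidence than the design allows.

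**Working it through.** **Blinding.** No figure is stated, so the check sets the statements side by side.

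| Claim | What the same section describes | Result |
|---|---|---|
| Experimenters fully blind | Researchers see per-participant performance in real time; the activities differ in kind and in whether difficulty changes | Unsupported for anyone who sees the feed; no separation from blinded staff is stated |
| Patients fully blind | Patients do one of two visibly different activities, after being given all study information | They know the activity; they can be blind only to which one is hypothesised to work |

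**Measurement.** Each listed outcome instrument, by source of the data:

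| Instrument | Role | Source |
|---|---|---|
| PSQI | primary | described as self-report |
| ISI | primary | perceived severity, rated by the patient |
| WHOQOL-BREF | primary | quality-of-life questionnaire |
| PROMIS global health | primary | self-perceived health |
| BRIEF-A | secondary | self-report format only |
| BDI-II | secondary | described as self-report |
| STAI (state) | secondary | described as self-report |
| PSWQ | secondary | items rated as typical of oneself |
| CAB | secondary | direct cognitive test |

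So 4 of 4 primary and 8 of 9 instruments overall are patient-reported. One is a direct test. None is completed by an associate; the BRIEF-A text restricts that instrument to the patient's own report. The sentence that all variables are measured both ways is therefore wrong for every primary outcome.

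The CAB gives limited reassurance. Its section says that, after the first administration, scores are recalculated from performance in the CogniFit training tasks, which the painting arm is not described as doing.

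**Illustration of size.** Inputs from Participant Selection and Sample Sizes: 60 per group, and two-sided 0.05, read from the 95% confidence interval and the bilateral test. The bias *b*, in SD units, is an assumption; the documents give none.

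With no true effect and a two-sample normal approximation, SE = √(2/60) = 0.1826 SD. The probability of a significant result favouring training is 1 − Φ(1.96 − *b*/SE).

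- *b* = 0.2: *b*/SE = 1.095; 1 − Φ(0.865) = 19.4%
- *b* = 0.3: *b*/SE = 1.643; 1 − Φ(0.317) = 37.6%
- Over a wider range, *b* = 0 / 0.1 / 0.4 / 0.5 gives 2.5% / 7.9% / 59.1% / 78.2%

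The two-sided t-test gives 19.2% and 37.1% at 0.2 and 0.3 SD.

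**The case against.** The strongest reply is that the text says patients are blind to the group classification, not to their activity. Someone who paints need not know that painting is the control. This stands as a possible reading. A reader might infer that patients must know they are controls; the documents do not show that. The consent sentence does not say that the hypothesis or the arm labels are disclosed. But unawareness of the hypothesis is a weaker property than full blinding, and the article does not say that the hypothesis is withheld.

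Second, the researchers who see the feed and the experimenters who are blind may be different people, and the article does not say exactly what the feed displays. A condensed article may leave role allocation to the full protocol, so its absence is not held against the plan. What remains is that the article makes an unqualified statement next to a procedure that conflicts with it.

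Third, a reader might infer that the weekly calls lead staff to encourage the trained arm more. Nothing supports this. The calls are described for participants generally, with one stated minimum, and no difference by arm is mentioned.

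Fourth, there is an active control over the same period, and Expected Results anticipates some non-specific improvement in it. This is a real strength. It removes expectation bias, however, only if expectations are equal between arms, and nothing described secures or checks that.

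Fifth, the article openly calls the PSQI a self-report questionnaire and does not rest its conclusions on objective sleep data. That is fair, and it makes the sentence on objective measurement an inaccurate summary that can be corrected by wording.

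**Conclusion.** The point holds as two misstatements. Full blinding of experimenters and patients is more than the described procedures support, and the statement that all variables are measured objectively is contradicted by the instrument list. Confidence in both is high, because they rest on the article's own text.

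The consequence is limited but matters for interpretation: expectation bias in the self-reported primary outcomes is not excluded by the stated blinding. Its size is unknown. The 19% to 37% range is not an estimate of this trial's false-positive rate, although a reader might take it as one. It depends wholly on an assumed 0.2 to 0.3 SD shift and on a simple two-group comparison, whereas the plan uses mixed models on pre-test and post-test data. It shows only that a modest bias would not be negligible at 60 per arm.

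The trial can be run as designed. The description should be corrected, and the conclusion worded to match.

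**What to change.** 1. Replace the full-blinding statement with the achievable claim: participants are not told which programme is hypothesised to work, and post-test administrators and the analyst are blind to arm.
2. Allocate existing staff so that those who see platform data or make the phone calls neither run post-tests nor analyse.
3. Correct the measurement sentence in Phase III: sleep and quality of life are self-reported only, and the CAB is the only direct test. Remove the reference to close associates, since no informant instrument is listed.
4. Word the conclusion as an effect on self-reported sleep.
5. Optionally, add one expectation item after the first session and one group-guess item at post-test, both reported by arm. These would show whether expectations were in fact similar; they are an improvement, not the correction of an error.

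Cost: changes of wording, minor role allocation within the existing team, and at most two short items. No extra patients or devices are needed. The downside is a less favourable blinding label.
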